### Concealment mechanism {16b}

Randomisation for the main trial will be completed by a central secure randomisation service hosted by the York Trials Unit, University of York. Randomisation will be completed via the Internet, with information recorded to check eligibility prior to randomisation. The randomisation system is designed and maintained by an independent data systems manager at the York Trials Unit, who is not involved in the recruitment of participants.

### Implementation {16c}

The allocation sequence for the main trial will be generated by the trial statistician who is independent of the recruiting sites and study researchers. This sequence will be implemented using the secure randomisation service that can be accessed by staff at the York Trials Unit and will assign participants to either expedited bathing adaptation or usual care.

## Assignment of interventions: blinding

### Who will be blinded {17a}

Researchers involved in obtaining informed consent and collecting data will not be informed of participant group allocation and will be blinded, as far as possible. However, due to the nature of data collection, it is not possible to ensure blinding. It will not be possible to conceal the allocation from the participants or from the adaptations or social care staff. The research team at YTU will also be aware of the allocation of participants for the purpose of the management of the trial.

### Procedure for unblinding if needed {17b}

Researchers who are unblinded to a participant’s allocation will be asked to record the source and details of the unblinding. Given the low-risk nature of this trial, and that the participant, coordinating centre and local authority will know the participant’s allocation, there will be no other circumstances where unblinding will be possible.

## Data collection and management

### Plans for assessment and collection of outcomes {18a}

Data will be collected at the following time points for both members of each pair (please see Figs. 1 and 2): (1) 4 weeks after the intervention participant receives their bathing adaptation, (2) 4 weeks after the control participant receives their bathing adaptation, or at 9 months (whichever is sooner) and (3) 12 weeks after the control participant receives their bathing adaptation or at 12 months (whichever is sooner).

**Fig. 1 Fig1:**
[figure not shown]
Participant flow through the study

**Fig. 2 Fig2:**
[figure not shown]
Schedule of enrolment, interventions and assessment. *Some participants enrolled early in the trial had an additional follow-up between t1 and t2 before the intervention was provided in the routine adaptation group. This follow-up has now been removed from the current version of the protocol

At baseline, participants who are able to answer questions themselves will complete a questionnaire comprised of participant demographics, property tenure, COVID-19 status and several outcome measures: the SF-36 [19, 20], number of falls, a health and social care service and resource use questionnaire, the EQ-5D-5L [21], the ASCOT questionnaire [16], the short Falls Efficacy Scale (FES) [22], the Barthel Index [23] and the bathing question of the Barthel Index [23]. If the participant lacks mental capacity, the alternative participant will complete a shortened questionnaire comprising participant demographics, property tenure, COVID-19 status and several outcome measures including number of falls, a health and social care questionnaire, the EQ-5D-5L (proxy version 2) [24], the Barthel Index [23], the bathing question of the Barthel Index [23] and perceived difficulty in bathing.

Similarly, at the three subsequent data collection time points, participants who are able to answer questions themselves will complete a questionnaire comprised of the SF-36 [19, 20], number of falls, a health and social care service and resource use questionnaire, the EQ-5D-5L [21], the ASCOT questionnaire [16], the short FES [22], the Barthel Index [23] and the bathing question of the Barthel Index [23]. If the participant lacks mental capacity, the alternative participant will again complete shortened questionnaire comprising a number of falls, a health and social care questionnaire, the EQ-5D-5L (proxy version) [24], the Barthel Index [23], the bathing question of the Barthel Index [23] and perceived difficulty in bathing.

Participants will be sent a ‘diary’ to complete following the first follow-up visit and after each subsequent follow-up visit to enable them to record contacts with health, social care and other services. This diary will be optional, for them to complete at home. The purpose is to aid their recall where there is a longer time period between each follow-up. The diary will not be returned to the research team.

### Plans to promote participant retention and complete follow-up {18b}

Participants will be sent a newsletter 6 months post-randomisation to maintain contact and promote engagement. The newsletter will be produced in collaboration with the PPI group and will thank participants for their time and involvement and have an FAQ section for possible queries that may arise. Where possible, we will aim to retain participants in the study for follow-up if they withdraw from the intervention.

### Data management {19}

All participant source data collected will be recorded on case report forms (CRF). This will be centrally monitored by the University of York’s Trials Unit. To ensure high-quality data, data collected within the case report forms will be processed at the York Trials Unit, using a licensed, automated, electronic system (Teleform) which allows data to be entered, checked and validated. Further details pertaining to the processing of the data will be documented in a study-specific data management plan.

Study documentation (both paper and electronic) will be retained in accordance with Good Research Practice and UK Law for 5 years after study completion in the Trial Master and Investigator Site Files, after which time information will be securely destroyed.

### Confidentiality {27}

Participants will be allocated a unique pseudo-anonymised ID number that they will keep throughout the trial.

Copies of paper documentation containing personal data will be stored at York Trials Unit, Newcastle University and the University of Nottingham. All data will be stored in a locked cupboard in a locked room with access to the cupboard restricted to the study team only. Identifiable and non-identifiable information will be stored separately. The key to the cupboard will be held by a data manager at York Trials Unit or designated study personnel at other study locations. Data stored electronically will only be accessible by password and only by individuals directly involved in the study.

### Plans for collection, laboratory evaluation and storage of biological specimens for genetic or molecular analysis in this trial/future use {33}

Not applicable. There are no biological specimens being collected in this trial.

## Statistical methods

### Statistical methods for primary and secondary outcomes {20a}

#### Statistical analysis

A detailed statistical analysis plan will be agreed upon with the joint Trial Steering Committee (TSC) and Data Monitoring Committee (DMC) prior to the completion of data collection. All analyses will be conducted using the principles of intention to treat (ITT), including all available randomised participants in the groups to which they were allocated, where data are available. Analyses will be conducted using two-sided statistical tests at the 5% significance level. The flow of participants through each stage of the trial will be presented in a CONSORT diagram. Baseline and outcome data will be summarised descriptively by treatment group and overall.

The primary analysis will compare the PCS score of the SF-36 [19, 20] between the two groups, excluding the group lacking the mental capacity to provide this, using a covariance pattern mixed linear regression model incorporating all post-randomisation time points, where effects of interest and baseline covariates are specified as fixed effects, and the correlation of observations within patients over time (random effect) is modelled by a covariance structure. The model will adjust for the treatment group, time, treatment group-by-time interaction, baseline PCS score and property tenure, with participant and site as random effects. Estimates of the difference between treatment groups in PCS scores will be extracted for all time points with a 95% confidence interval and *p*-value. The primary endpoint will be the treatment effect estimate at the first assessment time point (4 weeks post-fitting of the intervention participant adaptions) to evaluate the effect of adaptation versus no adaptation. We will also consider a linear regression analysis that compares data from the two groups taken 4 weeks after their shower adaptations have been installed (first follow-up for intervention group participants, second follow-up for those control group participants who have received their adaptation). This will allow us to investigate whether increased wait times impact the short-term effect of the intervention.

Other continuous secondary outcomes (e.g. SF-36 MCS, ASCOT, Barthel Index and FES-I) will be analysed using the same methods as the primary analysis; however, these analyses will also include those who could not complete the SF-36 at baseline. The number of falls experienced over the follow-up period will be compared between the groups using negative binomial regression adjusting for site and property tenure, and accounting for length of follow-up.

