### Sample size {14}

Studies examining the utility of the SF-36 across different clinical conditions have estimated the Minimum Clinically Important Difference (MCID) to be between 3 and 7 points [25–27]. This trial is powered to detect a conservative MCID of 4 points for our target population of older adults with a range of clinical conditions. The standard deviation of the SF-36 PCS in BATH-OUT-1 at baseline was 8 [14]. To detect a standardised difference of 0.5 with 80% power and 5% two-sided alpha and allowing for up to 45% non-collection of primary outcome data, and the inclusion of up to 15% of participants who lack the capacity to provide the primary outcome (based on data presented in the December 2022 Trial Steering Committee meeting), we will aim to recruit a total of 272 participants.

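### The primary model holds the baseline PCS slope equal at every follow-up, so it may under-adjust at follow-up 1, where the primary result is read; a baseline-by-time term removes the risk at almost no cost

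*Protocol article*

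**What the plan says.** Protocol article, Statistical methods for primary and secondary outcomes {20a}: the primary analysis is a covariance pattern mixed model over all follow-ups. Its terms are listed: "The model will adjust for the treatment group, time, treatment group-by-time interaction, baseline PCS score and property tenure". Participant and site are random effects. The covariance structure is not named, and a detailed analysis plan is to follow. The primary endpoint is the treatment effect at the first assessment.

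Outcomes {12} and Plans for assessment and collection of outcomes {18a}: follow-up 1 is set by the intervention participant's installation. Follow-ups 2 and 3 are set by the control participant's, the last being "12 weeks after the control participant receives their bathing adaptation or at 12 months (whichever is sooner").

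On missing data the article says two things. Sample size {14} is computed "allowing for up to 45% non-collection of primary outcome data". The section on non-adherence and missing data {20c} instead expects little missing data. It relies on the repeated-measures model to limit the impact and adds multiple imputation as a further assessment.

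**The concern.** The model lets the treatment effect differ by visit but not the baseline effect. Follow-up 1 is the visit nearest to baseline within each pair. Later visits can run to 12 months and are tied to the control participant's shower. If the baseline relation weakens over time, the later visits pull the common slope below the right value for follow-up 1.

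Two things could follow. Residual variance at follow-up 1 would be a little larger than necessary. And if the participants observed at follow-up 1 differ in baseline PCS between arms, a slope that is too shallow would remove only part of that difference and leave the rest in the primary estimate.

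**Working it through.** **The plan's own figure.** Sample size {14} gives: "This trial is powered to detect a conservative MCID of 4 points"; "The standard deviation of the SF-36 PCS in BATH-OUT-1 at baseline was 8"; "To detect a standardised difference of 0.5 with 80% power and 5% two-sided alpha".

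- Per arm: 2 × (1.960 + 0.842)² / 0.5² = 62.8, so 63 per arm and 126 in total (128 by the t-test).
- Inflated for 45% non-collection and 15% without capacity: 126 / (0.55 × 0.85) = 269.5, or 128 / 0.4675 = 273.8. The stated 272 lies between them.
- With capacity: 272 × 0.85 = 231. Analysed: 231 × 0.55 = 127.

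**Assumed inputs (not in the protocol).** The correlation r of baseline PCS with follow-up 1 is 0.5 to 0.8, either declining at later visits or constant. SD is 8 at each visit.

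**Formulas.** On the standardised scale, let b be the vector of visit-specific baseline slopes and V the covariance of the visits given baseline, with V_jk = R_jk − b_j b_k, where R is the between-visit correlation matrix.

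- Common slope = (1′V⁻¹b) / (1′V⁻¹1).
- Shortfall s = b₁ − common slope.
- Variance inflation at follow-up 1 = s² / (1 − r²).
- Bias in points = s × baseline imbalance in points among those observed.

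**Worked case.** Take r = 0.7 with slopes 0.70, 0.49, 0.343 and an unstructured covariance. V has diagonal 0.51, 0.760, 0.882 and off-diagonals V12 = 0.357, V13 = 0.250, V23 = 0.532. The weights 1′V⁻¹ / (1′V⁻¹1) are 0.669, 0.076, 0.254.

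- Common slope = 0.669×0.70 + 0.076×0.49 + 0.254×0.343 = 0.593.
- s = 0.107; inflation = 0.107² / 0.51 = 2.2%.
- Bias for a 2.3-point imbalance = 0.107 × 2.3 = 0.25 points.

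**Range.**

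| Setting | Shortfall | Variance inflation |
|---|---|---|
| Declining, unstructured | 0.06-0.17 | 0.9-3.7% |
| Declining, compound symmetry | 0.12-0.21 | 2.2-7.0% |
| Equal at all visits | 0 | 0 |

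Simulated fits with 231 participants, about 45% missing and correlations from 0.70/0.60/0.50 to 0.80/0.50/0.40 gave common slopes of 0.63-0.69 against 0.70-0.80 at follow-up 1. Variance was 1-5% higher. Losing lower-PCS participants more often in the intervention arm only produced the 2.3-point imbalance and a bias of 0.16-0.25 points, with about zero under visit-specific slopes.

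**Power with about 127 analysed.** At r = 0.5 it is 88.6-89.2% with the common slope and 90.2% with visit-specific slopes. At r = 0.7 it is 96.8-97.4% against 97.7%. The largest loss is 90.2 − 88.6 = 1.6 percentage points.

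**Bias by pattern of loss.** When loss was unrelated to baseline, the two models differed by 0.01 points. When it related to baseline in opposite directions by arm, with log-odds 0.5 per SD, the imbalance was 0.42 SD. The formula gives 0.107 × 0.42 × 8 = 0.36 points at r = 0.7, and the simulated difference was 0.36. At log-odds 1.0 the bias spans 0.3-1.2 points. It halves if only one arm is affected.

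**Declining slopes do not guarantee a shortfall.** With slopes 0.80/0.50/0.40 and between-visit correlation 0.7 throughout, V has diagonal 0.36, 0.75, 0.84 and off-diagonals V12 = 0.30, V13 = 0.38, V23 = 0.50. The unstructured common slope is then 0.797, which is almost exactly right for follow-up 1.

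**The case against.** A common-slope model is a valid specification: without arm-differential loss related to baseline, randomisation leaves no bias. The article is condensed, a fuller analysis plan is coming, and even the covariance structure is open. Visits are triggered by installations, and the Discussion reports longer waits in both groups, so one pair's follow-up 1 may fall later than another pair's follow-up 2. A decline by visit number is therefore not established. The multiple imputation in {20c}, if it uses baseline PCS and arm, would relax the common slope and could expose any bias.

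Most of this stands and limits the point. It does not remove it, because the article itself lists the model terms, and the imputation is a sensitivity analysis that leaves the primary estimate as it is.

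A reader might infer that the model definitely under-adjusts at follow-up 1, or that heavy loss makes the primary result biased. The protocol supports neither. It gives no baseline-to-follow-up correlations. The 45% is a planning allowance, at odds with the expectation in {20c}. Nothing shows that loss differs by arm.

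**Conclusion.** The point holds in conditional form and is minor. As written, one baseline PCS slope covers all follow-ups while the primary result is read at the first.

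- **Precision.** If baseline predicts follow-up 1 better than later visits, the cost is about 1-5% in variance, up to about 7% with compound symmetry, and nil if the relation is equal at all visits. Power stays above the planned 80% in every setting examined.
- **Bias.** It arises only if, in addition, loss relates to baseline PCS differently by arm. For a 2.3-point imbalance and follow-up 1 correlations of 0.7-0.8 with an unstructured covariance, it is roughly 0.15-0.25 points, or 4-6% of the 4-point target. That is about a quarter of the standard error: 8 × √(4 × 0.51 / 127) = 1.01 at r = 0.7. At the largest shortfall (compound symmetry) the same imbalance gives 0.21 × 2.3 = 0.48. Biases near 1 point need strong loss in opposite directions by arm.

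The correlations and loss patterns are assumptions throughout.

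**What to change.** Add a baseline PCS-by-time interaction to the primary model in {20a}, so that the follow-up 1 contrast uses its own baseline slope. Add the matching baseline-by-time term for each continuous secondary outcome analysed by the same method. Settle this in the analysis plan before data collection is complete.

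The cost is two degrees of freedom with three follow-ups, and one more if the early extra visit, since removed, is modelled as its own time point. No new data are needed and the target of 272 stands. If the slopes prove equal, only those degrees of freedom are spent.

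The two statements on expected missing data, in {14} and {20c}, should also be reconciled, although the change above does not depend on it.

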### Outcomes {12}

The use of pairwise randomisation means that the timing of the follow-up for each pair can be based on the completion of the bathing adaptations. For each randomised pair, participant follow-up data will be collected at three points: (1) 4 weeks after the intervention participant receives their bathing adaptation, (2) 4 weeks after the control participant receives their bathing adaptation or at 9 months (whichever is sooner) and (3) 12 weeks after the control participant receives their bathing adaptation, or at 12 months (whichever is sooner). For some participants recruited early in the study, data were collected 2 weeks before the planned installation date of the bathing adaptation in the control group participant, where possible; however, a protocol amendment was approved to remove this follow-up as the majority of participants were not completing this due to the dates of their showers being installed or difficulty getting the dates in time to schedule the follow-up. We will follow the majority of participants for 12 months; however, for the participants recruited at the end of the trial, we will follow them for 9 months (i.e., follow-up will continue for 9 months from the randomisation of the final participants).

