## Assignment of interventions: allocation

### Sequence generation {16a}

Eligible, consenting participants will be randomly allocated 1:1 to either the intervention (expedited bathing adaptation) or the usual care control group using the York Trials Unit secure web-based randomisation system. We will use ‘pairwise’ randomisation, at the level of the participant. Randomisation will be stratified by the capacity to complete the primary outcome. For those strata where the participant can complete the primary outcome, the randomisation is also stratified by site and property tenure (owner-occupied, local authority owned, privately rented including private and social landlords as one group), and for those who cannot, it will be stratified by site only. Randomisation will be stratified in this way as the primary analysis will exclude the group that was identified as being unable to complete the primary outcome at randomisation, and also as the wait for bathing adaptation can vary across sites and property tenures. After two participants within the same strata are recruited, they will be randomised together such that one will be allocated to the intervention group and the other to the control group, in a random order. We will do this so that we can follow both members of the pair up at the same time post-receipt of their adaptation to reduce the confounding effect of time to assessment. This is not the same as ‘matched’ randomisation.

Depending on the speed of recruitment, there is a risk that eligible participants may be left waiting to be randomised until another participant is available to pair with them. We shall limit the time participants wait to be randomised by allowing some flexibility for them to be paired, for example, with someone from a different property tenure within the same site and capacity. If a participant has not been randomised 3 weeks after consenting, they will be paired and randomised with any other participant who has consented at the same site. If, after 6 weeks, a participant has not been randomised, they will be paired and randomised with any other participant who has the capacity and has consented at any site. For those participants who are deemed not able to complete the primary outcome, they may be randomised using simple randomisation—without a pair, should the time waiting for a pair be too long.

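### The primary model has no term for the randomised pair, so if pair members remain alike after adjustment its intervals are slightly too wide

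*Protocol article*

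**What the plan says.** Sequence generation {16a} of the protocol article states: "We will use ‘pairwise’ randomisation, at the level of the participant". When two people in the same stratum are available, "they will be randomised together such that one will be allocated to the intervention group and the other to the control group". The aim is to "follow both members of the pair up at the same time post-receipt of their adaptation to reduce the confounding effect of time to assessment", and the section adds: "This is not the same as ‘matched’ randomisation". For participants able to complete the primary outcome, strata are formed by site and tenure. The rule is relaxed to anyone at the same site after 3 weeks without randomisation, and to anyone with capacity at any site after 6 weeks.

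Outcomes {12} explains that "the timing of the follow-up for each pair can be based on the completion of the bathing adaptations". The data collection section {18a} repeats that both members are assessed at times fixed by the intervention member's installation (first follow-up) and the control member's installation or a 9- or 12-month cap (second and third).

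The Statistical analysis section {20a} lists the primary model: fixed effects for group, time, group-by-time, baseline PCS and tenure, "with participant and site as random effects". The other continuous outcomes use the same method. Neither this section nor any other part of the article mentions a pair term.

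**The concern.** The article carries the stratification factors, site and tenure, into the model but leaves out the restriction that defines each allocation: two people, one per arm. The pair also sets when both are assessed. The authors regard time to assessment as capable of confounding the comparison, so they have themselves given a reason why two people assessed after the same interval might resemble each other more than two people from different pairs.

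Because each pair places one member in each arm, variation between pairs cancels from the within-pair difference. A model without a pair term leaves that variation in the error. If the residual correlation is positive, the reported standard error is larger than the true one. At stake is precision that the design has already provided, in a trial whose expected analysable sample only just gives 80% power.

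**Working it through.** **Inputs from Sample size {14}:** difference 4 points, SD 8, 80% power, 5% two-sided alpha, 45% non-collection, 15% without capacity, total 272.

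**Reproducing the stated size.** The normal approximation gives 63 per arm (126 in total) and the t-based calculation gives 64 per arm (128).
- 126 / 0.55 / 0.85 = 269.5
- 128 / 0.55 / 0.85 = 273.8

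These bracket 272. In reverse, 272 × 0.85 × 0.55 = 127 analysable, with power 0.80. No within-pair correlation enters, so the sample size does not depend on a gain from pairing.

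**Complete pairs expected.** 272 × 0.85 / 2 = 115.6 pairs with capacity. If loss is independent within pairs (assumed):
- complete pairs m = 115.6 × 0.55² = 35.0
- singletons per arm s = 115.6 × 0.55 × 0.45 = 28.6
- observed per arm n = m + s = 63.6

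**Formulas**, with ρ the residual within-pair correlation:
- standard error reported without a pair term: 8 × √(2/n)
- true standard error of that same estimate: 8 × √((2n − 2mρ)/n²)
- standard error with a random pair intercept: 8 × √(2/(m/(1 − ρ) + s))
- actual two-sided type I error without a pair term: 2Φ(−1.96 × reported/true)

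**Worked example, ρ = 0.10.** Reported: 8 × √(2/63.6) = 1.419. With the pair term: 35.0/0.90 + 28.6 = 67.5, so 8 × √(2/67.5) = 1.377. Ratio 1.419/1.377 = 1.030, an interval 3.0% too wide.

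**Planned 45% non-collection (m = 35.0, s = 28.6 per arm)**

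| ρ (assumed) | SE, no pair term | SE, pair term | Interval excess | Type I error, no pair term | Power without / with pair term |
|---|---|---|---|---|---|
| 0 | 1.419 | 1.419 | 0.0% | 5.0% | 0.805 / 0.805 |
| 0.05 | 1.419 | 1.399 | 1.4% | 4.7% | 0.808 / 0.816 |
| 0.10 | 1.419 | 1.377 | 3.0% | 4.4% | 0.812 / 0.827 |
| 0.20 | 1.419 | 1.330 | 6.7% | 3.8% | 0.819 / 0.852 |

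**Upper bound: all 127 analysed participants in complete pairs (m = 63.5, s = 0).** The ratio reduces to 1/√(1 − ρ).

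| ρ (assumed) | SE, no pair term | SE, pair term | Interval excess | Type I error, no pair term | Power without / with pair term |
|---|---|---|---|---|---|
| 0.05 | 1.420 | 1.384 | 2.6% | 4.4% | 0.810 / 0.824 |
| 0.10 | 1.420 | 1.347 | 5.4% | 3.9% | 0.817 / 0.844 |
| 0.20 | 1.420 | 1.270 | 11.8% | 2.8% | 0.831 / 0.883 |

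These figures treat the first follow-up as a single comparison of means with SD 8. The percentage excess does not depend on the SD, so ρ is read as the correlation left after adjustment for baseline PCS, site and tenure.

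**The case against.** The strongest reply is that little may be left for a pair term to explain. Site, tenure and baseline PCS are already in the model, and {16a} names site and tenure as the things across which waiting time varies. Pairs are expressly not matched, and the relaxed rules let some cross tenure or site. Under the planned missing data, many pairs would lose a member. All of this stands. It means the residual correlation could be small, and it is why the figures for 45% non-collection are the ones to use. It does not show that the correlation is zero: shared assessment and calendar timing remain, and where pairs cross tenure or site, those terms cannot stand in for pair.

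A second reply is that the analysis plan, which is not shown, may add a pair term. It may. But the article lists the model's fixed and random effects, so the omission is in what is stated.

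Stronger readings are tempting, and the documents do not support them:
- A reader might infer that the analysis ignores the unit of randomisation. It does not. The unit is the participant, who is in the model; the pair is a block of two, not a cluster.
- A reader might infer a false-positive risk or an underpowered trial. With zero or positive correlation, type I error is at or below 5%, and power without a pair term is still about 80% or more.
- A reader might infer that elapsed time varies widely between pairs, or that pair members are assessed on identical dates. The article gives no distribution of elapsed time and sets common target times only.

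**Conclusion.** The point holds as a modest loss of efficiency. It does not make the analysis invalid. Pairing is used to allocate and to schedule follow-up, and the stated primary model omits it. If the residual correlation is 0.05 to 0.20, intervals are about 1.4% to 6.7% too wide under the planned non-collection, with 2.6% to 11.8% as the ceiling.

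This rests on three assumptions that the article does not settle: the size of the correlation; that it is not negative, for which the article gives no reason; and, for the lower set of figures, that loss is independent within pairs. If members of a pair tend to be lost together, more of the pairs that remain are complete and the excess moves towards the ceiling.

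**What to change.** Add a random intercept for randomised pair to the primary model and to the secondary models that use the same method. Enter it as its own level, not only nested in site, so that cross-site pairs are handled. In the primary analysis, a participant whose partner has no data contributes as a singleton. In secondary analyses, participants without capacity who were randomised singly do the same. Use pair as the clustering unit in the CACE analysis.

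Do not add time from randomisation to assessment to the primary model. It is determined after randomisation by installation dates and the caps, so adjusting for it is not a neutral correction. Use it at most in a sensitivity analysis.

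The cost is one more variance component, estimated from units of at most two. It may come out at or near zero, in which case the model reverts to the planned one. No new data are needed, since follow-up is already scheduled by pair. Section {20a} has the analysis plan agreed before data collection is complete, so the change could be prespecified there.
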